## **2.5 Benefit/risk ratio**

Benefits:

We hypothesised that HDT15 would improve cerebral collaterals in patients randomised in the intervention group, which could subsequently reduce the ischemic injury and improve the clinical outcome. DOWN-SUITE aims to validate this hypothesis. Patients in the control group will expect no personal benefit or harm from participating in the trial as they will receive the standard recommended care.

Risks and constraints:

No harm from participating in DOWN-SUITE is expected for patients in the intervention or control groups. Previous clinical data on HDT15 raised no safety concerns. No difference in post-stroke complications, including cerebral oedema or haemorrhage, pneumonia or

mortality, was observed in a retrospective observational study. HDT15 is not expected to interfere with standard care, including the procedural steps of MT. Mild discomfort related to the tilted position may occur in some patients. The treating physician will continuously monitor all patients during the entire duration of the HDT15 application. No additional risk is expected in patients in the control group, as they will receive standard care.

Overall, this study's benefit/risk ratio is considered very favourable.

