#### 4.3.2 Secondary endpoints

Secondary endpoints will further assess:

i. **feasibility** outcomes:

- proportion of patients randomised to the intervention group who are able to maintain HDT15 during the entire MT procedure, encompassing patient tolerance, the ability to perform MT at -10° to -15° tilt and any other reasons for premature treatment termination;
- hospital admission-to-arterial access time (i.e. time to arterial puncture);

ii. **safety** outcomes:

- Mean values of systolic blood pressure, diastolic blood pressure and oxygen saturation from hospital admission to the end of MT; these physiological parameters will be monitored at entry in the Emergency Room, at entry in the angio suite and every 15 minutes from the start to the end of MT
- Proportion of patients presenting one or more episodes of vomiting from randomisation to the completion of MT
- Proportion of patients who had increase of  $\geq 4$  points on the NIHSS score within 24 $\pm$ 12 hours of the randomisation;
- Proportion of patients who had SICH per SITS-MOST definition within 24 $\pm$ 12 hours: type 2 parenchymal hematoma with neurological deterioration of  $\geq 4$  points on the NIHSS;
- proportion of patients with pneumonia within the first 72 hours after randomisation;
- Safety data, including serious and non-serious adverse events, as well as reasons for HDT15 discontinuation (e.g. discomfort, vomiting, neurological worsening, headache, respiratory distress) and technical challenges related to MT will be reported for both treatment arms;

iii. **efficacy** outcomes:

- functional outcome at 3 months, assessed with the ordinal score on the modified Rankin scale (shift across outcomes on the mRS between groups);
- early neurological improvement before MT, at 24±12 hours and at 7 days or discharge (whichever comes first), defined as percent change in NIHSS score  $[(\text{Admission NIHSS} - \text{time-point NIHSS}) \times 100 / \text{Admission NIHSS}]$ .

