### **5.4 Criteria for discontinuation of study procedure**

HDT15 will be discontinued in cases of patient-reported intolerable discomfort, observed severe discomfort in non-communicative patients, or at the treating physician's discretion for clinical reasons (e.g., vomiting). All reasons for discontinuation will be recorded and reported as safety data.

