## **6 EXPERIMENTAL STRATEGIES**

### **6.1 Study strategy: experimental group**

#### **6.1.1 Description of the strategy**

HDT15 will be applied in the intervention group in 2 different settings:

- in the Emergency Room, by tilting the stretcher to lower the head by -10° to -15° relative to the body of the patient; the degree of tilting will be checked using a dedicated digital inclinometer or a mobile phone app
- in the Angiography Suite, by tilting the angiography table to lower the head by -10° to -15° relative to the body of the patient, depending on the actual technology of the angiography system of each clinical site; the degree of tilting will be automatically checked using the angiography system

HDT15 will start as soon as possible following randomisation in the Emergency Room (i.e. after vascular neuroimaging), and will be maintained during the transfer to the Angiography Suite, as well as during the entire thrombectomy procedure: i.e. HDT15 will end after the completion of MT, when the patient is transferred from the angiography table to her/his bed in a standard flat position.

Application of HDT15 will not delay usual care. The standard in-hospital patient pathway, including transfer from neuroimaging room to the angiography suite and the required procedural steps of MT, will allow sufficient time for the application of HDT15. HDT15 duration is expected to be at least 30 minutes (estimated time 30 to 90 minutes), from start to the assessment of the primary efficacy endpoint.

The actual degree of HDT15 will be between -10° to -15°, depending on the ER stretchers and the angiographic system of each clinical site.

Despite conscious sedation being the preferred approach for MT in participating centers, for patients needing intubation, the HOB will be briefly set to 0° during tube placement to ensure safety, with immediate repositioning to the assigned position (HDT15: -10° to -15°; control: 0° to +30°) post-intubation to maintain protocol adherence.

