| NIHSS score                                                           | X                                    | X                                       | X                                                   |                                                            |
| TOAST classification                                                  |                                      |                                         |                                                     | X                                                          |
| AE and SAE records                                                    | X                                    | X                                       | X                                                   | X                                                          |
| Any reasons for HDT15 discontinuation                                             | X                                    |                                         |                                                     |                                                            |

 Including intracranial vascular imaging, may be performed using either CT or MRI

 Routine biological analyses: complete blood count, glycaemia, sodium, potassium hepatic profile, serum creatinine and lipid profile (at 24h only), C-reactive protein.

 Physiological parameters: blood pressure, heart rate, oxygen saturation at inclusion (at entry in the Emergency Room; at entry in the angio suite; every 15 minutes from the start to the end of MT) and at 24 hours

 NIHSS score at admission will be measured both before enrollment and immediately before MT.

 mRS, AE/SAE and TOAST classification at 90 days may be collected via phone by a trained coordinator if in-person visit is not feasible.

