#### ii. safety outcomes:

- Mean values of systolic blood pressure, diastolic blood pressure and oxygen saturation at entry in the Emergency Room, at entry in the angio suite and every 15 minutes from the start to the end of MT; they will be treated as continuous variables and calculated as mean with their 95% confidence interval for each group.
- Proportion of patients presenting one or more episodes of vomiting from randomisation to the completion of MT will be calculated with their 95% confidence interval for each group.
- Reasons for HDT15 discontinuation (e.g., intolerable discomfort, observed severe discomfort in non-communicative patients, vomiting, neurological worsening,

headache, or respiratory distress), minor adverse events, and MT-related technical challenges will be recorded and reported as proportions with 95% confidence intervals.

- The proportions of patients who had an increase of  $\geq 4$  points on the NIHSS score within  $24 \pm 12$  hours of the randomisation will be calculated with their 95% confidence interval for each group.
- The proportions of patients who had SICH within  $24 \pm 12$  hours will be calculated with their 95% confidence interval for each group.
- The proportions of patients with pneumonia within the first 72 hours after randomisation will be calculated with their 95% confidence interval for each group.
- Safety data, including serious and non-serious adverse events, as well as reasons for HDT15 discontinuation (e.g. discomfort, vomiting, neurological worsening, headache, respiratory distress) and technical challenges related to MT will be reported for both treatment arms. Adverse events will be categorized according to the Medical Dictionary for Regulatory Activities (MedDRA) v28.0.

iii. **efficacy** outcomes:

- functional outcome at 3 months, assessed with the ordinal score on the modified Rankin scale (shift across outcomes on the mRS between groups).
- Percent change in NIHSS ( $[(\text{Admission NIHSS} - \text{time-point NIHSS}) \times 100 / \text{Admission NIHSS}]$ ) from admission to immediately pre-MT, at  $24 \pm 12$  hours, and at  $7 \pm 2$  days (or discharge), calculated with 95% confidence intervals.

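### No blood pressure or oxygen saturation reading is scheduled between the start of tilt and angio-suite entry, so patients who stop HDT15 before suite entry contribute only off-tilt values

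*Protocol*

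**What the plan says.** Protocol 4.3.2 defines a safety endpoint of mean systolic pressure, diastolic pressure and oxygen saturation over the period that opens at hospital admission and closes when MT ends. Readings are due "at entry in the Emergency Room, at entry in the angio suite and every 15 minutes from the start to the end of MT".

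Footnote 3 of the summary table in 7.2 gives the same schedule, "at entry in the Emergency Room; at entry in the angio suite; every 15 minutes from the start to the end of MT", and adds heart rate and a reading at 24 hours. Section 9.3.3 repeats the time points and reports a mean with a 95% confidence interval for each group.

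On the exposure, 6.1.1 says "HDT15 will start as soon as possible following randomisation in the Emergency Room (i.e. after vascular neuroimaging), and will be maintained during the transfer", which means the move to the angiography suite. It also says "HDT15 will end after the completion of MT".

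Section 5.4 allows tilt to be stopped for intolerance or at the treating physician's discretion, and adds: "All reasons for discontinuation will be recorded and reported as safety data". Section 2.5 promises bedside oversight: "The treating physician will continuously monitor all patients during the entire duration of the HDT15 application".

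**The concern.** The point is when readings are taken, not how they are summarised. Tilt begins in the emergency room, but the schedule records nothing under tilt until the patient reaches the angio suite. From the start of MT it records every 15 minutes. The endpoint's stated period therefore contains a stretch of exposure with no scheduled observation.

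This matters most for a patient who becomes unstable in the emergency room or in transit and is returned to a standard position. The saturation and pressure that led to the stop are not among the scheduled values, while the values taken after the stop still enter the HDT15-arm summary. The means can then look calmer than the tilt experience of the patients who tolerated it least. A later analysis plan could change the summary, but it could not supply readings that nobody was asked to record.

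The protocol itself treats this phase as one of risk. Vomiting is counted from randomisation, respiratory distress is a named reason for stopping, and low saturation and severe respiratory or cardiac disease are exclusions. Section 2.6 names transferred and prehospital patients as the next targets, and their exposure would lie largely outside an angio suite.

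**Working it through.** The protocol states no figure for this point, so the check places the scheduled readings on the tilt timeline.

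**Step 1. Order of events (6.1.1, 7.3.2, 4.3.2).**

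| Event | Scheduled reading? | Tilt status in the HDT15 arm |
|---|---|---|
| Emergency room entry | Yes | Before tilt |
| Imaging, consent, randomisation | No | Before tilt |
| Tilt starts in the emergency room | No | On tilt |
| Remaining emergency room time and transfer | No | On tilt |
| Discontinuation, if any | No | Change from on to off |
| Angio-suite entry | Yes | On tilt only if not yet stopped |
| MT, every 15 minutes | Yes | On tilt only if not yet stopped |
| 24 hours (7.2 footnote 3) | Yes | Off tilt for everyone |

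No reading falls between the start of tilt and suite entry.

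**Step 2. On-tilt readings by time of stopping.** The protocol gives no phase durations, so these are assumptions: suite entry 15 to 45 minutes after tilt starts, MT starting 0 to 15 minutes after suite entry, and MT lasting 60 minutes with readings at 0, 15, 30, 45 and 60 minutes. Post-randomisation readings up to the end of MT = 1 (suite entry) + 5 (MT) = 6.

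| Tilt stopped | Readings taken on tilt | Count |
|---|---|---|
| Before suite entry | none | 0 of 6 |
| 1 minute after suite entry | suite entry, plus MT start if MT starts at once | 1 to 2 of 6 |
| 20 minutes into MT | suite entry, MT 0 and 15 | 3 of 6 |
| 45 minutes into MT | suite entry, MT 0, 15, 30 and 45 | 5 of 6 |

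The zero in the first row does not depend on the assumed durations. It follows from the order of events alone. The other rows show that the problem is confined to stops before suite entry.

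**Step 3. Could another provision supply the missing values?**

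- Continuous monitoring (2.5) has no recorded time point attached to it.
- Section 7.3.2 has blood pressure monitoring written in the medical record, but gives no emergency room times and does not mention saturation there.
- Section 14.1 limits the eCRF to data needed for the protocol and publication, so unscheduled values have no assured route into the dataset.
- Section 5.4 captures the reason for stopping, not the values at that moment.
- The exposure analysis in 9.3.2 needs head angle and duration for each patient, so position has to be tracked through this phase. Pressure and saturation are not scheduled alongside it.

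**Step 4. Size.** The effect on an arm mean depends on the share of patients who stop before suite entry and on how far their on-tilt values differ from those recorded. The protocol gives neither. It also gives no emergency-room-to-suite time, so the length of the unsampled interval is unknown.

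**The case against.** The strongest reply is that this is a gap in recorded numbers, not in observation. Patients are watched throughout tilt, adverse events are sought from the first visit (8.2.1), vomiting is counted from randomisation, and reasons for stopping, including respiratory distress and neurological worsening, are reported. A stop in the emergency room would therefore be visible in the results. That stands. What it does not supply is the depth of the change, or comparable values from the control arm over the same phase.

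It can also be said that the schedule is stated consistently in three places, that the summary is descriptive and by group, that values after stopping properly belong in a by-group summary, and that sampling frequency in a proof-of-concept trial is a judgement. All of that is fair. It makes this an improvement to data capture rather than a contradiction. Even so, the schedule does not cover the period the endpoint claims to describe.

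Two stronger readings are tempting and are not supported:

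- A reader might infer that everyone who stops early contributes only off-tilt values. The counts above show otherwise for stops at or after suite entry.
- A reader might take the 30 to 90 minutes in 6.1.1 as the unsampled interval and count the 15-minute readings it lacks. That period runs to the angiographic assessment, which 4.3.1 places at the first procedural step of MT. It therefore includes time in the suite after the entry reading, and the true gap is shorter by an unknown amount.

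Timing also limits the gain. Section 7.1 plans 15 months of inclusion from the third quarter of 2024. Five quarters later is the fourth quarter of 2025, and version 4 is dated 18/08/2025, so on the planned timetable much of the enrolment may already be past.

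**Conclusion.** The concern holds in a limited form. The schedule has no blood pressure or saturation reading between the start of tilt and angio-suite entry, although the endpoint claims the whole period from admission. Patients who stop HDT15 before suite entry contribute 0 on-tilt readings, and the change that led to stopping is not recorded as a value, although the event and its reason are. This rests only on the stated order of events.

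The size of the effect on the arm means cannot be computed from the protocol, and any number of affected patients would be a guess. Nor can it be inferred that patients go unobserved in this phase, since monitoring and event reporting continue. The consequence is a physiological safety summary that is selective towards patients still tilted on reaching the suite. It does not affect the primary endpoint.

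**What to change.** In 4.3.2, 7.2 footnote 3 and 9.3.3, add blood pressure and oxygen saturation from the existing bedside monitor, in both arms:

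1. just before the assigned position starts;
2. at least once in the assigned position before suite entry, where time allows;
3. at any discontinuation of the assigned position.

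Flag every reading as on or off the assigned position, and summarise the pre-MT phase separately from the MT phase in 9.3.3. This changes data capture and reporting only and leaves every clinical rule as it is.

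The cost is a few eCRF fields and a sentence in each of three sections, with no extra procedure because monitoring is already in place. The downside is a few more values to transcribe in a time-critical phase, and no gain for patients already enrolled. The version record lists a fourth amendment that is still undated, which may be a convenient vehicle. If the change comes during enrolment, report how many patients were enrolled before and after it.

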#### 3.2 Secondary objective

The secondary objectives of the present study are:

- Assessment of the **feasibility**: proportion of those who are able to maintain HDT15 position during the MT procedure; time delay between hospital admission and arterial puncture for MT in both the intervention and control groups;
- **Safety**: physiological parameters (blood pressure, oxygen saturation) from hospital admission to the end of MT; vomiting from neuroimaging to the end of MT; neurological deterioration within 24±12 hours; occurrence of symptomatic intracranial haemorrhage (SICH) within 24±12 hours (see definition in paragraph 4.3.2); occurrence of pneumonia with the first 72 hours; these safety outcomes will be assessed in both the intervention and control groups
- **Clinical efficacy**: neurological outcome at 3 months in the HDT15 compared to the control group, assessed with the modified Rankin Scale (mRS).

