### **7.3.3 Follow-up visits**

- **Visit 2 – Day 1 (24 ± 12 hours)**

Clinical study visit at 24 hours, performed by a neurologist, will consists of a clinical and neurological examination (NIHSS score), an assessment of serious adverse events, and routine blood chemistry tests (including complete blood count, sodium, potassium, glycemia, Hba1c, total bilirubin, alkaline phosphatase, alanine et aspartate transaminase, gamma-glutamyl transferase, serum creatinine, troponin and C-reactive protein and lipid profile).

A second neuroimaging (either brain CT or MRI), part of the routine follow-up of acute ischemic stroke patients, will be performed to control the evolution of stroke and detect early complications (such as SlCH).

- **Visit 3 – Day 7 ± 2 days or hospital discharge**

At Day seven or at hospital discharge (whichever comes first), the clinical study visit, performed by a neurologist, will consists of a neurological (NIHSS score) examination and an assessment of serious adverse events.

- **Visit 4 – Day 90 ± 15 days**

This will be the last visit of this trial. Clinical study visit by the neurologist at 90 days will consist of a standardised assessment of neurological disability (mRS score), the evaluation of stroke etiology (TOAST score), and an assessment of serious adverse events.

If a clinical visit can't be performed, a phone call will be scheduled in order to collect the mRS score and the serious adverse events.

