### **8.2.4 Restriction of AEs/SAEs and reporting period of AEs/SAEs**

Given that the study is being conducted in patients with acute ischemic stroke, restrictions on the notification of SAEs to the safety sector of clinical trials have been put in place to account for adverse events which are expected as part of the natural history of the patient population under study.

***Restriction of SAEs (SAE notification form not to be immediately sent to the DSMB but only to be collected in the CRF at the latest at the end of the study participation):***

- *Adverse events related to the procedure (HDT15) under study:*  
There is no expected serious adverse event related to HDT15 in the intervention group of patients.
- *Adverse events related to the disease under study (acute ischemic stroke):*
  - ⇒ Death (as it is expected from epidemiological data),
  - ⇒ Hemorrhagic transformation of the ischemic lesion,
  - ⇒ Stroke recurrence,
  - ⇒ Malignant cerebral infarction,
  - ⇒ Early neurological deterioration,
  - ⇒ Cardio circulatory arrest,
  - ⇒ Cardiogenic shock,
  - ⇒ Myocardial infarction,
  - ⇒ Heart failure,
  - ⇒ Acute pulmonary edema,
  - ⇒ Pulmonary embolism,
  - ⇒ Pneumonia,
  - ⇒ Urinary tract infection,
  - ⇒ Atrial fibrillation,
  - ⇒ Severe arterial hypertension, defined as blood pressure over 180/110 mmHg.
- *Adverse events related to MT and/or intravenous thrombolysis:*
  - ⇒ Arterial dissection,

- ⇒ Artery perforation,
- ⇒ Vasospasm,
- ⇒ Stent occlusion,
- ⇒ Intracranial hemorrhage (sICH), either symptomatic or not,
- ⇒ Cerebral or systemic embolism,
- ⇒ Facial angioedema,

The investigator should notify the sponsor any serious adverse events, not included in the above specified ones, without delay:

- *FROM THE PATIENT'S INCLUSION (date of signature of the 1st consent)*
- *Until the END OF THE PATIENT'S PARTICIPATION*
- No time limit for serious adverse events related to the research (e.g. cancers, congenital malformations occurring in the long term after exposure to the investigational medicinal product...).

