### **9.3 Statistical methods**

#### **9.3.1 General considerations**

The quantitative variables will be described by the following parameters: number of patients, number of missing values, mean, standard deviation (SD), median, first and third quartiles (Q1 and Q3), minimum and maximum. Categories could be defined if applicable using a cut-off threshold from literature or quantiles.

The qualitative variables will be described by the following parameters: number of patients, number of missing values, frequency and percentage of each modality (missing values will not be included in the denominator used for frequency computation).

The analyses will be performed using the R and SAS software. They will be performed by the biostatistics unit of the University of Milano-Bicocca.

After the end of the statistical analysis of the DOWN-SUITE study, a meta-analysis could be carried out with the French partner ([name], Hospices Civils de Lyon), who applied for funding for a similar study (DOWN-SUITE-Fr, the result of which is pending).

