#### **9.5 Method of taking missing data into account**

Analyses will be performed on data available. There will be no imputation of missing data.

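### The spelled-out SICH definition has no alternative for death, so a type 2 haematoma that kills before the 24±12 h NIHSS cannot be counted in either arm

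*Protocol*

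**What the plan says.** Protocol 4.3.2 lists among the safety outcomes the "Proportion of patients who had SICH per SITS-MOST definition within 24"±12 hours. After a colon it spells the definition out: "type 2 parenchymal hematoma with neurological deterioration of" 4 or more NIHSS points.

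This is the only SICH definition in the protocol. The safety objective in 3.2 points back to it ("see definition in paragraph 4.3.2"). The analysis in 9.3.3 ("The proportions of patients who had SICH within" the window) gives a proportion with a 95% confidence interval for each group, and says nothing about death.

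Four other places bear on how a fatal case is handled:

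- **NIHSS timing.** The notes to the 7.2 table put the admission scores before enrolment and immediately before thrombectomy. The next score is at Visit 2 (7.3.3), at 24±12 hours, where follow-up imaging is also scheduled.
- **Missing data.** Section 9.5 states: "There will be no imputation of missing data".
- **Denominators.** For categorical variables, 9.3.1 states that "missing values will not be included in the denominator used for frequency computation".
- **Safety reporting.** Section 8.2.4 exempts death, haemorrhagic transformation and intracranial haemorrhage from immediate notification but keeps them in the CRF. Sections 4.3.2 and 9.3.3 report adverse events for both arms.

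**The concern.** The definition joins an imaging finding to a change in a clinical score, and a dead patient cannot be scored. Read literally, a type 2 haematoma followed by death before the 24±12 h examination meets the first criterion and can never meet the second. The rule therefore leaves out the most severe form of the event that it is meant to detect.

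SICH is the only bleeding endpoint in 4.3.2, and mortality is not listed there as a safety endpoint of its own. The adjacent endpoint, an NIHSS increase of at least 4 points, has the same gap, so one early fatal bleed can be missed by both. Because 9.3.3 plans rates by arm and no test, the absolute rate is what readers will take from the trial, and an under-count goes straight into it.

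**Working it through.** **1. Arm size.** The only figure that the protocol states here is the sample size in 9.1: 60% versus 35%, two-sided alpha 0.05, power 80%, 59 per group. With the unpooled normal approximation,

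n = (1.960 + 0.842)² × (0.60×0.40 + 0.35×0.65) / 0.25² = 7.849 × 0.4675 / 0.0625 = 58.7,

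which rounds up to 59, with power 80.2% at 59. The figure reproduces. It supplies the denominator below and has no other bearing on SICH, for which the protocol states no rate, margin or power.

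**2. Following one fatal case through the text.** A patient is randomised, treated, imaged with a type 2 haematoma, and dies before the Visit 2 examination.

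- Imaging criterion (4.3.2): met.
- NIHSS criterion (4.3.2): cannot be shown, because no score is scheduled between the one just before thrombectomy and Visit 2.
- Imputation (9.5): none.
- Classification: not stated. Either the case is coded as no SICH and stays in the denominator, or it is missing and leaves the denominator under 9.3.1.

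Both routes lose the case from the numerator.

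**3. Size per case.** If the denominator stays at 59, each lost case costs 1/59 = 1.7 percentage points.

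**4. Illustration.** The protocol gives neither a SICH rate nor an early fatality rate, so the counts here are assumed. Take 4 true cases in an arm of 59, of which f die before scoring. The rate is (4 − f)/59 if coded as no SICH and (4 − f)/(59 − f) if dropped. Exact (Clopper-Pearson) 95% intervals are in brackets.

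| f | Deaths counted | Coded as no SICH | Dropped as missing |
|---|---|---|---|
| 0 | 4/59 = 6.8% (1.9 to 16.5) | same | same |
| 1 | 6.8% | 3/59 = 5.1% (1.1 to 14.1) | 3/58 = 5.2% (1.1 to 14.4) |
| 2 | 6.8% | 2/59 = 3.4% (0.4 to 11.7) | 2/57 = 3.5% (0.4 to 12.1) |
| 3 | 6.8% | 1/59 = 1.7% (0.0 to 9.1) | 1/56 = 1.8% (0.0 to 9.6) |

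The choice between coding and dropping moves the rate by about 0.1 point. The loss from the numerator moves it by about 1.7 points per case.

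**5. Between arms.** If the same fraction of true cases is lost in each arm, both rates shrink by that fraction: the ratio is kept and the difference narrows. The ratio is distorted only if early lethality differs by arm, and the documents contain nothing on that.

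**The case against.** **The operative definition is the named one.** The protocol cites SITS-MOST, and the words after the colon may be only a short paraphrase. The full source wording is not in the documents, so it cannot be said here whether it covers death. That stands, and it is why the fix includes a check against the source. The spelled-out text is still what sites and programmers have in front of them, and 3.2 sends readers to it.

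**Classifying early deaths belongs in the SAP.** This would hold for a coding detail. The protocol, however, states the case definition itself, and an SAP should not have to add a criterion to it.

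**The group is narrow.** Follow-up imaging and NIHSS fall at the same visit, so the patient must be imaged at or before it and die before being examined. This stands: the number is probably small.

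**The events are not lost to the trial.** Deaths and haemorrhages are collected in the CRF, adverse events are reported by arm, and the DSMB reviews accumulating data (8.4). This stands too. The gap is in the SICH line and not in the whole safety record.

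**Stronger readings that the documents do not support.** A reader might infer that these patients will be recorded as no SICH. The protocol does not say so, and 9.3.1 with 9.5 could equally make them missing. A reader might also infer that the definition hides harm from head-down tilt in particular. It applies identically to both arms, and nothing suggests that early fatal bleeds differ between them. One can construct counts in which an imbalance disappears, for example 5/59 versus 2/59 becoming 2/59 in each arm if three tilt cases are fatal early. That lethality is assumed, and the full counts would themselves be weak evidence (Fisher p = 0.44; intervals 2.8 to 18.7% and 0.4 to 11.7%).

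**Conclusion.** The concern holds as a defect in the stated case definition. Followed literally, 4.3.2 cannot count a type 2 haematoma that kills before the 24±12 h NIHSS, so the only listed bleeding endpoint can under-count the gravest bleeds in either arm. At 59 per arm the effect is about 1.7 percentage points per uncounted case, under either way of handling the missing score.

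This rests on three assumptions: that the spelled-out text is what will be applied, that no unscheduled NIHSS is recorded before death, and that the safety denominator is close to the planned 59. How many cases would be affected is unknown. No directional bias between arms is shown. The point deserves correction because the omission runs one way and the repair is simple, although the endpoint is descriptive and the events remain visible in the adverse event data.

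**What to change.** In 4.3.2, define SICH as a type 2 parenchymal haematoma on imaging within the window, together with either an NIHSS increase of at least 4 points or death. Carry the same definition into 9.3.3 by reference. When making the change, check the spelled-out text against the named SITS-MOST definition so that the two agree. It would also help to say how a death before scoring is treated in the adjacent NIHSS-increase endpoint, and to show deaths beside SICH by arm.

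The cost is one phrase, which could go into the fourth amendment that the version record in 1.2 lists without a date. No new data are needed: the core lab already reads follow-up imaging (10.1), and deaths are already recorded (8.2). The only downside is that the reported SICH rate may be slightly higher.
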